## Abstract

The current treatment for the autoimmune disease of hypothyroidism (AIDH) is based on pharmacotherapy with levothyroxine. A non-pharmacological supplementary element of therapy could be the implementation of an individualized balanced diet and probiotics. *Lactiplantibacillus plantarum 299v* (*Lp299v*), with its anti-inflammatory effects, may also support the therapy. However, the number of studies on personalized dietary interventions with probiotics in AIDH is limited, and no clear conclusions can be drawn from the results so far. Therefore, this trial will analyze the effect of *Lp299v* supplementation in conjunction with nutrition education on the quality of life and nutritional status of patients with Hashimoto’s. Methods: This double-blind, 12-week intervention study will include 100 female patients with AIDH. They will be divided into two groups: (1) individual personalized nutrition education + *Lp299v* and (2) individual personalized nutrition education + placebo. Before and after the education intervention, selected elements in the diet, eating behavior, quality of life, nutritional status (anthropometric parameters, body composition), blood pressure, and anti-TPO (antibodies against thyroid peroxidase) titer will be assessed. Hypothesis: It is expected that this study will provide deeper knowledge on the validity of using proper nutritional principles and *Lp299v* in AIDH. Specifically, the impact on the subjective assessment of the quality of life, selected elements in the diet, and the state of nutrition and health will be assessed.

## 1. Introduction

The autoimmune disease of hypothyroidism (AIDH, Hashimoto’s thyroiditis) affects an increasing number of people, particularly women [1]. In the course of this disease, many symptoms and health consequences arise that worsen the quality of life [2]. Hypothyroidism worsens the motility of the gastrointestinal tract, which may lead to disorders such as dyspepsia, IBS (irritable bowel syndrome), or SIBO (Small Intestinal Bacterial Overgrowth) [3,4]. Hypothyroidism may also increase the risk of obesity [5], which is associated with a positive anti-TPO (antibodies directed against thyroid peroxidase) titer [6]. Patients with AIDH are more likely to have excess body mass compared to those without the disease [5], which increases the risk of hypertension—the most important risk factor for ischemic heart disease, stroke, other cardiovascular diseases, chronic kidney disease, and dementia [7]. On the other hand, subclinical hypothyroidism may also occur during the course of AIHD, increasing the risk of hypertension, especially in middle-aged women, although the mechanism is not fully understood [8]. The treatment for AIHD mainly involves the patient taking levothyroxine for life [2].

The medical treatment of AIDH can be supplemented by a balanced diet containing important anti-inflammatory nutrients. Selenium and vitamin D reduce the anti-TPO and anti-TG antibodies (antibodies directed against thyroglobulin) characteristic of AIDH [9,10,11,12,13,14]. In addition, selenium and iodine are key elements in thyroid hormone synthesis, and their deficiency can lead to hypothyroidism [15,16,17]. Zinc, copper, and iron also affect the production of thyroid hormones [18]. A low iron status results in less efficient use of iodine and thyroid hormone synthesis, leading to hypothyroidism [17,19]. In addition, iron-deficiency anemia is correlated with a higher frequency of anti-TPO antibodies [20]. Recent reports indicate that the higher the serum magnesium level, the lower the titer of anti-TG antibodies [21]. Literature reviews have mainly focused on the impact of nutrients on Hashimoto’s thyroiditis, with few articles on the type of diet that would be most beneficial [22]. Most often, patients are recommended an anti-inflammatory, balanced diet, with the Mediterranean diet being the most recognizable example. Ruggeri et al. [23] observed that adhering to the Mediterranean diet was associated with a lower odds ratio of developing thyroid autoimmunity. The anti-inflammatory diet has also found applications in systemic lupus erythematosus [24], multiple sclerosis [25], psoriasis [26], and rheumatoid arthritis [27].

A diet that is especially rich in fermented food products and drinks containing probiotic bacteria has been associated with health benefits, such as a reduced risk of high blood pressure [28] and obesity [29]. There is growing evidence of the beneficial effects of probiotics, not only on the intestinal microbiota but also on overall health, including immune health [30]. Unfortunately, the number of studies on the impact of probiotic therapy on Hashimoto’s thyroiditis is unsatisfactory. In a blinded study conducted by Talebi et al., a synbiotic blend was used, consisting of four strains of the genus *Lactobacillus,* two strains of the genus *Bifidobacterium*, *Sreptococcus thermophilus*, and fructooligosaccharide. This blend showed no significant effect on anti-TPO [31]. Another study examined the effects of a synbiotic (500 mg of 10^9^ CFU/g probiotics plus fructooligosaccharide) on adult hypothyroid patients [32]. Although a 10-week supplementation had no beneficial effects on serum thyroid-stimulating hormones, it did result in improved blood pressure and quality of life among patients with hypothyroidism [32]. Hashimoto’s thyroiditis is characterized by an increased inflammatory burden, accompanied by increased red cell distribution width. The latter increases in iron deficiency anemia but is also associated with conditions characterized by overt or subclinical inflammation [33]. On the other hand, nutritional status and indexes, such as the prognostic nutritional index (PNI), are also associated with inflammatory conditions, such as infections [34] and diabetic microvascular complications [35]. Thus, the effects of altering nutritional status via probiotic bacteria in Hashimoto’s thyroiditis are worthy of further study.

Based on a wide search of the literature, it was found that the data on dietary interventions and probiotic therapy for AIDH are unsatisfactory. Furthermore, it is difficult to determine the efficacy of effective probiotic therapy in AIDH, especially since the results of studies on specific strains cannot be extrapolated to other strains of the same species that have not been tested in patients with AIDH. In addition, no studies were found on interventions consisting of rational nutrition in combination with probiotic therapy (*Lactiplantibacillus plantarum 299v*) in individuals with AIDH aimed at improving their diet, nutritional status, and quality of life. Therefore, this study will provide further data on this relatively unexplored area of research.

## 2. Study Aim and Hypothesis

The primary objective of the trial is to assess the effect of a dietary intervention with probiotic *Lp299v* supplementation on body weight and quality of life in female AIDH patients.

The secondary objective of the trial is to evaluate the effectiveness of individual personalized nutritional counseling on several key parameters among patients diagnosed with Hashimoto’s thyroiditis. The specific focus areas for assessment include food selection and diet quality, body composition, serum anti-TPO, and blood pressure.

The research hypotheses are as follows:-Individual personalized nutrition education aimed at improving food selection and diet quality may enhance nutritional status, anti-TPO parameters in the blood, and the overall quality of life in AIDH patients.-The *Lp299v* strain may augment the impact of the individual nutritional intervention, particularly in terms of improving the quality of life, body weight status, and anti-TPO parameters in the blood.

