### 3.2. Selection of Participants

The selection of the sample for the study will be purposive, taking into account the inclusion and exclusion criteria. Recruitment for the study will be carried out using the snowball method, mainly via social networking sites (i.e., internet websites associated with Hashimoto’s patients). Additionally, collaboration with medical facilities and pharmacies will be established to reach a broader pool of potential participants. The CAWI (Computer-Assisted Web Interview) and PAPI (Paper and Pen Personal Interview) methods will be used for collecting data.

The inclusion criteria will be a medical diagnosis of Hashimoto’s disease based on anti-TPO, anti-TG, or an ultrasound image characteristic of AIDH; thyroid function status (euthyroid, hypothyroidism); female; age in the range of 18-64 years; normal body weight (body mass index BMI 18.50–24.99 kg/m^2^) or excessive body weight (BMI ≥ 25.00 kg/m^2^); and/or low-quality diet (low Pro-Healthy Diet Index (pHDI-10)) [36]. Women with contraindications to a body composition analysis performed using the electrical bioimpedance method (i.e., having a pacemaker) will also be included. However, for these patients, the body composition analysis stage will be skipped.

The exclusion criteria will be thyroid diseases other than AIDH, pregnancy, lactation, diagnosed cancer, and lack of consent to participate in the study. The individual must not take *Lp299v* or medications for weight loss or be diagnosed with celiac disease, Duhring’s disease, or a gluten allergy. The minimum number of subjects (47 for each group) was calculated based on an expected 50% improvement in the overall quality of life after 12 weeks of the intervention in the experimental group, with an assumed 5% significance level and 80% power. The baseline sample size of 100 patients was established to account for potential participant withdrawals.

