### 3.7. Quality of Life

The quality of life of the participants will be assessed using the Quality of Life Questionnaire for Patients with Thyroid Diseases (ThyPROpl).

ThyPROpl is a thyroid-specific questionnaire validated for the Polish population by Sawicka-Gutaj et al. [38]. The questionnaire comprises 85 questions grouped into 13 scales measuring aspects of quality of life relevant to thyroid patients. The 13-point scale includes questions on (1) symptoms, (2) feeling tired, (3) energy, (4) memory and concentration, (5) nervousness and tension, (6) mental well-being, (7) problems with coping or mood swings, (8) relationships with other people, (9) daily activities, (10) sex life, (11) the impact of the disease or its treatment on appearance, (12) the intensity of the impact of the disease on the subject in general. All quality-of-life questions will cover the last 4 weeks prior to the survey. The respondents must choose 1 of 5 answer categories: (1) not at all, (2) a little, (3) average, (4) quite a lot, (5) very much. In the question regarding difficulties in performing duties at work, the authors added an additional category—“I do not work” [38]. The score ranges from 0 to 100, with higher scores indicating a poorer quality of life.

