### 3.13. Statistical Analyses

All statistical analyses will be conducted using Statistica 13.1 PL (StatSoft Inc., Tulsa, OK, USA; StatSoft, Krakow, Poland). Categorical variables will be presented as a sample percentage (%). Continuous variables will be presented as means with 95% confidence intervals (95%CIs) for variables with a normal distribution or medians with an interquartile range (IQR) for variables with a non-normal distribution. To assess the impact of the nutritional intervention with probiotic supplementation and verify the differences between the experimental and control groups, multivariate analysis of variance and two-tailed tests will be applied. The normality of the variable distribution will be assessed using the Shapiro–Wilk test before statistical analysis. For continuous variables, e.g., diet quality scores, scores of quality of life, markers of adiposity, metabolic parameters, and changes after 12 weeks of education relative to baseline, will be assessed using a *t*-test for dependent samples for normally distributed variables or a Mann–Whitney test for variables without a normal distribution. Differences in categorical variables will be examined using the Pearson chi-squared test. *p* < 0.05 will be considered statistically significant.

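### Two unranked primary outcomes share one flat 5% threshold, so the error rate of the primary claim is up to 9.75% if success on either outcome counts

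*Protocol article*

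**What the plan says.** Four places in the protocol article bear on this.

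- **Section 2 (Study Aim and Hypothesis).** The primary objective concerns the effect of the intervention with probiotic "supplementation on body weight and quality of life in female AIDH patients". Neither outcome is placed first, and no success rule is given. Diet quality, body composition, anti-TPO and blood pressure come under the secondary objective.
- **Section 3.2 (Selection of Participants).** The minimum of 47 per group is derived for one outcome, overall quality of life, "with an assumed 5% significance level and 80% power". Body weight has no planning figure.
- **Section 3.7 (Quality of Life).** On the instrument: "The questionnaire comprises 85 questions grouped into 13 scales measuring aspects of quality of life relevant to thyroid patients". The numbered list that follows has 12 entries. On scoring: "The score ranges from 0 to 100, with higher scores indicating a poorer quality of life". Whether this range belongs to each scale or to a composite is not stated.
- **Section 3.13 (Statistical Analyses).** For the group comparison, "multivariate analysis of variance and two-tailed tests will be applied". The variables to be tested include "scores of quality of life", in the plural. The threshold is p "< 0.05 will be considered statistically significant", with no allocation, hierarchy or adjustment.

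**The concern.** With two primary outcomes and a single unadjusted threshold, a trial of an ineffective probiotic has two chances to produce a significant primary result. Unless both are required, or one is tested before the other, the 5% level used in section 3.2 does not describe the error rate of the primary conclusion.

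The quality-of-life outcome adds a second layer. The overall quality of life in the sample size paragraph is not tied to a named score. It could be a composite, the last listed scale (which concerns the overall impact of the disease), or a judgement across all scales. If the choice is made after the data are seen, or if every scale is tested, there are more routes to a positive claim.

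At stake is whether a reader can take a significant primary result at its stated level.

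**Working it through.** **Inputs from the protocol article.** Two primary outcomes (section 2); alpha 0.05 and two-tailed tests (section 3.13); 13 scales stated and 12 listed (section 3.7); 47 per group, 5%, 80% power, quality of life only (section 3.2). The document gives no correlations, so those below are assumptions.

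**1. The plan's own figure.** The 47 per group can be neither confirmed nor refuted, because no standard deviation, baseline mean or control rate is given. Read as a two-sided comparison of means, it implies a standardised difference of (1.960 + 0.842) × √(2/47) = 0.578. A standardised difference of exactly 0.5 would need 63 per group two-sided, or 50 one-sided. Read as proportions, 50% against 22% needs 45 and 50% against 23% needs 49. The error-rate argument does not depend on which reading is right. All of these readings size a single outcome at 5%.

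**2. Two primary outcomes, either one sufficient.**

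- Independent tests: 1 − 0.95² = 0.0975, or 9.75%.
- Correlated test statistics (simulation, 200,000 draws): 9.0% at correlation 0.5 and 7.0% at 0.9.

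**3. Two primary outcomes, both required.** The error rate of the joint claim is at most 5%, so there is no inflation. Power would then also depend on body weight, for which nothing was planned.

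**4. Body weight plus every scale tested separately.** This is a scenario that the document leaves open. It is not a stated plan.

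| Tests | Assumed correlation among scales | Family-wise error |
|---|---|---|
| 14 (weight + 13 scales) | 0, all independent | 1 − 0.95¹⁴ = 51.2% |
| 13 (weight + 12 listed scales) | 0, all independent | 1 − 0.95¹³ = 48.7% |
| 14, weight independent of the scales | 0.3 | 44.6% |
| 14, weight independent of the scales | 0.5 | 36.8% |
| 14, weight independent of the scales | 0.7 | 27.8% |

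**5. Candidate remedies.**

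- *Bonferroni, 0.025 each:* 1 − 0.975² = 4.94%. If 47 per group gives 80% power at 0.05 (difference 0.578), power per outcome at 0.025 is 71% with 47 per group and 74% with 50. Restoring 80% needs 57 per group before withdrawals.
- *Fixed sequence, quality of life first:* each test is at 0.05 and the family-wise error is at most 5%. If quality of life has no effect, any false claim must first pass its 5% test. If it has an effect, only the body weight test can err, at 5%.

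**The case against.** **Both outcomes may be required.** Section 2 joins body weight and quality of life with a plain conjunction. If both must be significant, there is no inflation. This is a fair reading, but the document does not state it, so the 9.75% has to remain conditional on either outcome sufficing.

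**The multivariate analysis of variance could protect the level.** It can test several outcomes jointly at 5%. It would limit the inflation only if the individual tests depended on it, and section 3.13 does not say so. It also does not say which outcomes enter it.

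**The details may be in a full analysis plan.** Scoring rules and multiplicity procedures are often left there, and their absence from an article is no defect in itself. What stands is narrower. The article itself fixes two unranked primary outcomes and one flat threshold, and sizes the trial for a single outcome at 5%. These do not fit together as written.

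**A reader might infer an error rate of about 50%.** The documents do not support that as the headline. It needs all 13 scales to be separate primary outcomes and all 14 tests to be independent. No section makes the scales primary, and section 3.2 points to one overall score. Scales of one questionnaire answered by the same women are likely to be positively correlated. The 51% is a ceiling. Even the 28% to 45% range applies only if the scales are in fact tested one by one.

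**A reader might also infer that everything except one score should become exploratory.** Section 2 lists its secondary outcomes explicitly, and nothing here is a reason to demote them.

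**Conclusion.** The point holds in a limited form. Sections 2 and 3.13 together allow a primary claim from either of two outcomes, each judged at 5%, with no allocation, hierarchy or both-must-succeed rule. On that reading the family-wise error is up to 9.75%, or about 7% to 9% at assumed correlations of 0.9 to 0.5, against the 5% used in section 3.2. If both outcomes were required, the inflation would vanish.

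The error is larger if the quality-of-life scales are tested separately, which remains possible because no section names the overall score. The size of that excess depends on correlations that the document does not give.

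The mismatch between 13 stated and 12 listed scales is an editorial correction. It moves only the independence ceiling, from 51.2% to 48.7%.

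**What to change.** 1. In sections 2 and 3.7, name one overall ThyPROpl score and state how it is formed. Make its between-arm comparison at week 12 the first primary test, at two-sided 5%. This agrees with section 3.2, which sizes the trial on overall quality of life.
2. Test body weight second, at two-sided 5%, only if the first test is significant. State this order in section 3.13, and say what part the multivariate analysis of variance plays in it.
3. Report the individual scales as supportive, with confidence intervals.
4. Leave the secondary outcomes of section 2 as secondary.
5. Make the stated number of scales agree with the list in section 3.7.

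**Cost.** Only text changes; no extra patients or measurements. Body weight loses its independent route to a primary claim. If the trial does have the planned 80% power for quality of life, one trial in five would stop before the body weight test even when the assumed effect is real. Quality of life keeps the full 5%, but whether its power is truly 80% cannot be verified, because the 47 per group cannot be reproduced from the information given.

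If the sponsor wishes to keep body weight as an equal primary outcome, a Bonferroni split or a both-must-succeed rule would also hold the level. The first lowers power per outcome to about 71% at 47 per group under the implied difference. The second needs a planning figure for body weight.

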## 3. Materials and Methods

### 3.1. Study Design and Ethical Approval

We plan a 12-week single-center, double-blind dietary intervention in which AIDH patients will be randomly allocated into two groups: experimental and control. Participants in the experimental group will receive individual personalized nutrition education along with the probiotic *Lactiplantibacillus plantarum 299v*, while in the control group, *Lp299v* will be replaced by a placebo. The form of the administered supplement (capsule) will be identical in both cases; neither the researcher nor the patient will have knowledge of its contents. The detailed schedule of the trial is presented in the following section. All visits for measurements and data collection will take place at the Dietetics Counselling Center, Department of Dietetics, Faculty of Human Nutrition, Warsaw University of Life Sciences. All tests performed during the intervention will be provided free of charge to the participants, who will not receive any financial benefits or cost reimbursements for participating in the study.

The study protocol was registered with and approved by the Ethics Committee for Research with Human Participation at the Institute of Human Nutrition Sciences, Warsaw University of Life Sciences, in compliance with the principles of ethics (Resolution No. 22/2021 and No. 21/2022). The study will adhere to the Declaration of Helsinki, and all participants will provide informed consent. Each participant will be presented with a detailed description, and any questions or concerns will be addressed. Participants will be informed that they may withdraw at any stage from the study without providing a reason. It is important to note that side effects of *Lactiplantibacillus plantarum 299v* are rare and do not pose a threat to the patient. To ensure participant retention, direct contact with the researcher will be available throughout the study period.

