### 3.4. Course of Intervention

The 12-week intervention will involve individual nutrition education for patients with Hashimoto’s thyroiditis conducted in two groups. One group will additionally receive the *Lp299v* strain (NE + *Lp299v* group), and the other will receive a placebo (NE + P group). Before the start of education, an assessment of dietary habits will be performed using a three-day food record questionnaire. Additionally, validated tools will be used to assess (1) the dietary habits and nutritional beliefs (FFQ-6 and KomPAN^®^ questionnaire [36,37]); (2) the quality of life with thyroid diseases (ThyPROpl) [38]; (3) physical activity level (Polish version of IPAQ questionnaire) [39]. Anthropometric measurements (body weight and height, waist and hip circumferences), body composition, peripheral arterial pressure, and anti-TPO blood concentration measurements will also be performed. All parameters will be measured twice: at baseline and after 12 weeks of the intervention to evaluate changes and (if possible) compare the measurements to reference values. A diagram of the study is presented below (Figure 1).

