### 3.11. Nutrition Education

Nutrition education is planned for 12 weeks, with 6 individual meetings spaced about 2 weeks apart. There will be a total of 6 h of education in the entire program. The form of meetings will be online or in person, depending on the patient’s preferences. At the beginning of the education intervention, the patient will be presented with an interpretation of her eating habits, the nutritional value of her diet, and her nutritional status. A personalized goal (e.g., weight loss in the case of a patient with obesity) that the patient should achieve will also be discussed and set. During the education intervention, the following issues, among others, will be discussed with all participants: nutritional recommendations and essential nutrients (role, sources in food) in Hashimoto’s thyroiditis; factors affecting iron bioavailability; glycemic index and glycemic load—application and importance; weight reduction assumptions; snacking—causes and tips on how to minimize the need to reach for snacks; mindful eating; “Healthy eating plate”—nutritional recommendations for the Polish population presenting the correct proportions of individual product groups in a daily diet [53]; interactions between levothyroxine and food; the importance of microbiota in HT; *Lactobacillus plantarum 299v*—impact on human health based on scientific research (mainly on the immune system, iron, intestinal symptoms, blood pressure); and myths and facts about nutrition in HT. In addition to the above-mentioned topics, participants will be able to receive answers to individual questions/concerns.

All educational materials will be prepared based on the scientific literature and standards by The Polish Society of Dietetics and the National Public Institute—National Institute of Hygiene. Each participant will receive educational materials and a sample menu depending on energy needs to illustrate how meals and portions should look. Throughout the entire study period, participants will have the possibility of consulting with a dietitian, who will also support the introduction of changes in eating habits depending on individual personalized needs.

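### The secondary objective and hypothesis 1 ask whether nutrition counselling works, but both arms receive it, so only uncontrolled before–after change can speak to them

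*Protocol article*

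**What the plan says.** Section 2 of the protocol article gives the secondary aim: "The secondary objective of the trial is to evaluate the effectiveness of individual personalized nutritional counseling on several key parameters". The parameters listed are food selection and diet quality, body composition, serum anti-TPO and blood pressure. Hypothesis 1 runs in the same direction: "Individual personalized nutrition education aimed at improving food selection and diet quality may enhance nutritional status", together with anti-TPO and quality of life. Hypothesis 2 concerns the probiotic, which "strain may augment the impact of the individual nutritional intervention", particularly for quality of life, body weight status and anti-TPO.

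Section 3.1 describes the arms: "Participants in the experimental group will receive individual personalized nutrition education along with the probiotic" strain, while for controls the strain "will be replaced by a placebo". Section 3.4 confirms that education goes to everyone: "The 12-week intervention will involve individual nutrition education for patients with Hashimoto’s thyroiditis conducted in two groups". Section 3.11 says of the education topics that "the following issues, among others, will be discussed with all participants".

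Section 3.4 schedules all measurements twice, at baseline and after 12 weeks. Section 3.13 plans a comparison of the experimental and control groups. It also plans a test of 12-week change from baseline, by a dependent-samples t-test where the variable is normally distributed. The limitations listed in section 4 cover the way the group is selected, self-reported intake and the spacing of meetings. They do not mention the lack of a comparator without education.

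**The concern.** To evaluate the effectiveness of counselling is to ask what would have happened without it. In this design nobody goes without it: there is no untreated arm, waiting list, run-in period or external control. A whole stated objective and one of the two hypotheses can then be addressed only by uncontrolled change over 12 weeks.

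That change has several possible sources besides education. Every woman takes a capsule, and section 3.11 teaches all of them about the reported health effects of Lp299v, so expectation is present in both arms. In the experimental arm the probiotic itself is mixed in. Diet is self-reported after coaching on diet. Medication and supplements are recorded (section 3.6), but nothing in the design separates their influence. Section 3.2 allows entry on a low pHDI-10, and a score chosen for being low tends to be higher when measured again.

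At stake is what the trial may conclude. A before–after difference in anti-TPO, blood pressure or diet score could be taken as evidence from a randomised trial that counselling works in Hashimoto's disease, although randomisation contributes nothing to that statement.

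**Working it through.** **Step 1: what differs between the arms.**

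| Component | Experimental arm | Control arm | Difference |
|---|---|---|---|
| Nutrition education (3.1, 3.4, 3.11) | all | all | none |
| Capsule (3.1, 3.12) | Lp299v | placebo | the randomised contrast |
| Measurements (3.4) | baseline, week 12 | baseline, week 12 | none |

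Exposure to education is 100% versus 100%. The between-arm comparison therefore estimates the effect of Lp299v added to education, which is hypothesis 2. It holds no information on hypothesis 1 or on the secondary objective as worded, at any sample size.

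**Step 2: the plan's own figure.** Section 3.2 gives 47 per group at 5% significance and 80% power. It cannot be reproduced, because the article gives no standard deviation, control-arm response or sidedness. With a two-sided test, 47 per group corresponds to a standardised between-arm difference of (1.960 + 0.842) × √(2/47) = 0.578. The present point does not rest on this figure; 47, and 2 × 47 = 94 for both arms pooled, serve below only as numbers of patients.

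**Step 3: how often a paired test rejects when education does nothing, any outcome.** Let g be the mean change from other causes, in SDs of the change score (assumed). By the normal approximation, the rejection probability of a two-sided 5% test is Φ(g√n − 1.96) + Φ(−g√n − 1.96).

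| g | n = 50 (one arm) | n = 100 (pooled) |
|---|---|---|
| 0 | 5% | 5% |
| 0.1 | 11% | 17% |
| 0.2 | 29% | 52% |
| 0.3 | 56% | 85% |

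The part of g that is common to both arms cancels in the comparison of Lp299v with placebo.

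**Step 4: regression to the mean alone, pHDI-10 only.** Assumptions, none of them in the article: the enrolled women average G source-population SDs below the source mean at baseline; test–retest correlation r is 0.6 to 0.8; education has no effect; the SD of change is √(2(1 − r)), which ignores any narrowing of baseline spread through selection.

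- Expected shift = (1 − r)G
- Standardised change dz = (1 − r)G / √(2(1 − r))
- Example with G = 1 and r = 0.6: shift 0.4, dz = 0.4/0.894 = 0.447
- Rejection probability from the noncentral t distribution, two-sided 5%, noncentrality dz√n

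| G | r | Shift (SD) | dz | n = 47 | n = 94 |
|---|---|---|---|---|---|
| 0.3 | 0.6 | 0.12 | 0.134 | 15% | 25% |
| 0.3 | 0.7 | 0.09 | 0.116 | 12% | 20% |
| 0.3 | 0.8 | 0.06 | 0.095 | 10% | 15% |
| 0.5 | 0.6 | 0.20 | 0.224 | 32% | 57% |
| 0.5 | 0.8 | 0.10 | 0.158 | 19% | 33% |
| 1 | 0.6 | 0.40 | 0.447 | 85% | 99% |
| 1 | 0.7 | 0.30 | 0.387 | 74% | 96% |
| 1 | 0.8 | 0.20 | 0.316 | 56% | 86% |

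The normal approximation gives 26% in place of 25% in the first row. With G = 0 the rate is the nominal 5%.

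**The case against.** Giving education to everyone is a legitimate add-on design. Randomisation, blinding and the Lp299v comparison are untouched, and reporting change within arms is ordinary practice. All of this stands, and it keeps the point at the level of what is claimed.

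A reader might go further in four ways that the article does not support.

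- **The primary objective is untestable too.** Section 2 words it loosely, as a dietary intervention with a probiotic. Hypothesis 2, the description of the arms in section 3.1 and the between-group comparison in section 3.13 together make the contrast Lp299v versus placebo on top of education, and the design tests that.
- **The randomised question is missing for the secondary outcomes altogether.** Hypothesis 2 names anti-TPO, and the between-group sentence in section 3.13 is not restricted to primary outcomes. What is missing is an objective in these terms.
- **False improvement is near certain.** The 56 to 99% range needs an average entry gap of 1 SD. Section 3.2 joins low pHDI-10 to the weight criterion by and/or, so not every woman need have a poor diet score. The calculation also does not carry over to the other outcomes: no entry cut-off is set for blood pressure or body composition, and anti-TPO is one of three alternative diagnostic routes.
- **The trial will report counselling as proven.** The hypotheses say only that education may help, and section 3.13 says only that changes will be assessed. Misreading is a risk created by the stated objective, the planned test and a limitations section without a caveat; it is not an announced intention.

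It is also fair to say that nobody expects a capsule to change food choice, and hypothesis 2 does not claim it. A between-arm comparison of diet quality is therefore of less interest than the others, but it remains the only comparison there that randomisation protects.

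**Conclusion.** The point holds for the secondary objective and hypothesis 1. The design cannot test either, because both arms receive the same education, measurements are taken only at baseline and week 12, and the only randomised contrast is Lp299v versus placebo. This follows from the article alone, and an analysis plan that is not shown could not supply the missing comparator.

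How far before–after change would mislead is unknown. The percentages illustrate the range under assumed entry gaps and correlations, and the conclusion does not depend on them. The consequence is confined to interpretation of a secondary objective and one hypothesis, so this should be fixed, but it does not threaten the main comparison.

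**What to change.** - **Section 2, secondary objective:** restate it for diet quality, body composition, anti-TPO and blood pressure as the between-arm effect of Lp299v versus placebo added to nutrition education. This agrees with hypothesis 2, which already names anti-TPO.
- **Section 2, hypothesis 1:** reword it as an expectation about change observed during education, without a claim of effect.
- **Section 3.13:** label before–after change under education, including change in diet quality, as descriptive, with no conclusion on effectiveness.
- **Section 4, limitations:** add that there is no comparator without education.
- **Section 2, primary objective:** saying explicitly that it is Lp299v versus placebo on top of education would be a useful tidy-up of wording only.

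The cost is rewording. Sample size, visits and data collection stay as they are. The downside is that a causal claim about education is given up. Keeping that claim would require a comparator without education, for example a 2 × 2 factorial design, with a new sample size for which the article gives no inputs.
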